### Data Flow Display

[figure not shown]

## **9 ETHICAL, LEGAL AND ADMINISTRATIVE ASPECTS**

### **9.1 Data Quality Assurance**

The Sponsor will conduct a site visit to verify the qualifications of each Investigator, inspect the site facilities, and inform the Investigators of responsibilities and the procedures for ensuring adequate and correct documentation.

The Trial Site Principal Investigator of each trial site will conduct a site visit to verify the qualifications of each Investigator. Before beginning the study there will be an Investigator meeting for training on the protocol, GCP, etc.

Each study center will be attended by a clinical monitor. The clinical monitor is qualified by his/her training and experience to oversee the conduct of the study. The principle Investigators and the Investigators agree with and support the monitoring procedure as described in the protocol.

The Investigator is required to prepare and maintain adequate and accurate case histories designed to record all observations and other data pertinent to the study for each study participant. All information recorded in the CRF for this study must be consistent with the patients' source documentation (i.e., medical records).

To ensure data quality and completeness the following will be adhered to:

- Fully documented Individual Case Safety Reports (ICSRs) in the data base
- Diligent follow-up of each case
- Retain reporter's verbatim AE terms (documenting any Sponsor differences)
- Consistent and accurate codification of reported terms.

The responsible person in the central stem cell laboratory will be primarily responsible for the quality and safety of the cell product. The quality control and safety data will be subject to secondary post-hoc monitoring by the Clinical Monitor. Should the Clinical Monitor detect a violation of the quality control and product release standards, he/she will exclude the patient from the study and immediately inform the local Investigators so that appropriate medical measures can be taken.

The general coordination of the pooling for the study will be performed by the Coordinating Investigator [name]. med. [name] from the University of Rostock.

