The randomization code will be stored by the Statistician. Only the members of Team A will have access to the randomization code. All members will sign an agreement, stating that the randomization code will be kept confidential and no person outside the trial Team A will have access to the code.

At each site sealed emergency envelopes will be stored at a secure place containing the randomization code. In case of an emergency which requires knowledge of treatment the treatment code for an individual patient can be revealed to a member of Team B (treatment team) by opening the sealed envelope. See Section 5.4 for details of breaking the blind.

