### 5.4 Blinding and Breaking the Blind

The study will be performed in a double-blind manner. The appearance of the final placebo and cellular product will be indistinguishable to the Investigators. Cell

concentrations of  $0.2$  to  $2.0 \times 10^6$  are not detectable by pure vision in the type of syringes used for application. The patients will be blinded to the treatment they receive. The surgeons and the Investigators involved in the preoperative and postoperative assessments will be blinded regarding the treatment group assignment (Team B). Only the laboratory personnel involved in the cell isolation process will not be blinded (Team A).

Team A (cell processing team) will be responsible for the preparation of the medicinal product as well as for the preparation of the placebo control and for randomization. This team will not be involved in patient recruitment/selection, clinical assessment, data collection or the treatment/sham injection. These unblinded team members should not reveal the identity of the study medication at any time.

Team B (treatment team) will be responsible for the patient recruitment/selection, clinical assessment, data collection, bone marrow harvest, and will perform the treatment/sham injection. The members of Team B will be unaware of the randomization code and blinded to the treatment.

In case of an emergency, and necessity for breaking the code, an emergency envelope will be available 24 hours a day, 7 days a week for a member of Team B. When breaking the code, a member of Team B will sign and date on the emergency envelope which has been unblinded. The treatment code for an individual patient can be revealed to a member of Team B only in case of an emergency, which requires knowledge of treatment. At the end of the trial all emergency envelopes will be returned to the Statistician and will be checked for integrity of the seal.

The study blind should not be broken except in a medical emergency (where knowledge of the study drug received would affect the treatment of the emergency) or regulatory requirement (e.g., for serious adverse events [SAEs] or death).

The investigator should promptly document and explain to the sponsor any code breaking (e.g. accidental unblinding, unblinding due to a serious adverse event) of the investigational product. If the blind is broken, the date, time and reason must be documented in the patient's CRF, and any associated AE report.

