#### 5.9.1 *CD133+ Cell Product Release criteria*

To ensure consistent quality and individual safety of the cell product, it will only be released if the following specifications regarding the validated manufacturing process have been met:

- A. Minimum number of CD133+ cells =  $0.1 \times 10^6$  cells
- B. Maximum number of CD133+ cells =  $5 \times 10^6$  cells
- C. Minimum depletion of non-target cells = 2.5 log (> 99.6%)
- D. Minimum percentage of viable cells = 80%
- E. Manufacturing and Quality Control according to GMP

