#### *6.3.1.4 Follow-Up of Adverse Events*

All AEs experienced by a patient, irrespective of the suspected causality, will be monitored until the event has resolved, any abnormal laboratory values have returned to baseline or stabilized at a level acceptable to the Investigator and the Clinical Monitor, until there is a satisfactory explanation for the changes observed, or until the patient is lost to follow-up.

After class II to IV AEs, patients will remain hospitalized until complete stabilization. The institutions/physicians following the patients during and after convalescence will be informed about the patient's study participation and advised to increase their level of attention. The study center Investigator will conduct safety-related follow-up examinations on an outpatient basis for a minimum of 6 months or until resolution of these AEs.

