### 7.2.2 *Bone Marrow Transfer /Preparation of Cell Product/Placebo (Assessment Ia; Day -2 to 0)*

- Bone marrow aspiration and 20 mL blood sample collection for preparation of autologous serum (see Section 5.8). Transferring data in form "Transfer Protocol":
  - Serologic data (seronegative/seropositive)
  - Date and time of bone marrow harvest
  - Bone marrow volume (mL)
  - Date and time of blood sample taking
  - Blood sample volume
  - Date, time of start (handover to carrier) and end of transport from OP to stem cell laboratory

- Transfer of cells to the stem cell laboratory for processing
- Randomization to study treatment group performed by the cell processing laboratory
- Cell/placebo preparation according to validated SOPs
- Transfer of investigational drug from stem cell laboratory to OP with "Transfer Protocol"
- Documentation of data in "Transfer Protocol"
  - Date, time of start and end of transport from stem cell laboratory to OP at study site
  - Date and time of receiving investigational drug at OP, department, names of study nurse and physician
  - Confirmation of receipt of sealed randomization code envelope
  - Copy of "Transfer Protocol" into CRF
- Documentation of any change in concomitant medication
- Documentation of any AE/SAE since last assessment
- Data transfer into "Cell Preparation Form" to be performed after last patient out only:
  - Allocation of randomization No. to CD133+ cell preparation group or placebo group
  - Volume of bone marrow aspirate after filtration (200 µm) in mL
  - Volume of "final product" after resuspension in saline/autologous serum in mL
  - Recovery of CD 133+ cells in "final product" compared to bone marrow
  - Log depletion of non-target cells
  - Total viable CD 133+ cells in 5 mL syringes ("Final product ready for injection")
  - Bacterial contamination: results of quick test and sterility test

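### Section 9.1 lets the Clinical Monitor exclude patients and alert sites on cell-product quality data, and this is not reconciled with the blinding, follow-up and full-analysis-set rules

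*Protocol*

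**What the plan says.** Section 9.1 makes the responsible person in the stem cell laboratory primarily responsible for product quality. It adds a secondary review by the Clinical Monitor, described as post hoc but not dated. The consequence of a finding is fixed: "Should the Clinical Monitor detect a violation of the quality control and product release standards, he/she will exclude the patient from the study", and the monitor must "immediately inform the local Investigators so that appropriate medical measures can be taken". The same section says: "Each study center will be attended by a clinical monitor".

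Other sections bear on this:

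- **Blinding (5.4, 4.5).** "Only the laboratory personnel involved in the cell isolation process will not be blinded (Team A"). Team members also sign that "no person outside the trial Team A will have access to the code". The protocol names some other holders or routes (the Statistician who stores the code, the emergency envelopes, the Safety Monitoring Board). The monitor is not among them.
- **Release criteria (5.9.1).** Of the CD133+ cell product it says that "it will only be released if the following specifications regarding the validated manufacturing process have been met". The list covers cell count, depletion, viability and GMP manufacture.
- **Preparation data (7.2.2).** Entry of the allocation, recovery, depletion, viable cells and contamination results into the Cell Preparation Form is "to be performed after last patient out only".
- **What the physician hears (3.3, 5.9.3).** A yield from 0.1 to below 0.5 million cells goes to the Statistician and is kept from physician and patient. If a product is not released, the physician is told.
- **Analysis (8.1.2, 8.1.3, 8.2).** Major violations for the Per Protocol Set are defined at a blind review meeting. Low-count patients are excluded but still followed. The FAS holds every randomized patient in the allocated group. Missing values are not replaced.

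**The concern.** The monitor is a site-facing role. Under sections 9.2 and 9.3 the monitor checks CRFs against source at the site. Under 6.3.1.3 the monitor reviews all adverse events with the Investigator at each visit. Under 6.3.1.4 abnormal laboratory values are followed until they have returned to baseline or "stabilized at a level acceptable to the Investigator and the Clinical Monitor". Section 9.1 gives this role records that may show which product a patient received, and orders a message to Investigators who are meant to be blinded.

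Two things are at stake. First, Investigators who grade NYHA and CCS class, run the walk test and judge causality could infer the arm from the message. Second, one person can remove a randomized patient on a product-quality finding, outside blind review and with no instruction to obtain the 6-month MRI.

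**Working it through.** No figure in the plan supports or refutes this point. The plan's own sample size was checked only for context. With a difference of 4.5, SD 7.5 and n = 60 per group, the non-centrality is √(60/2) × 4.5/7.5 = 3.29 and the power is 0.903. Then 60/0.85 = 70.6, which rounds up to 71 per group, or 142 in total. The stated figures reproduce and the point does not change them.

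**Sections side by side**

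1. *Who sees what.* Sections 4.5 and 5.4 make Team A the unblinded group. Section 9.1 gives product quality data to someone outside it. Nothing says that the person reviewing product quality differs from the monitor who attends the site, or that the records are stripped of allocation.
2. *When.* Section 7.2.2 holds back entry into one form until the last patient is out. Section 9.1 expects immediate notice so that something can be done for the patient, but does not date the review or name its source records. Whether the monitor works from that form or from laboratory records is left open.
3. *What the site is told.* Section 3.3 keeps a low yield from the physician. Sections 3.3 and 5.9.3 have the physician told when a product is not released. Section 9.1 has the Investigators told of a violation found later, with no rule on content.
4. *What happens to the patient.* Section 8.1.2 excludes low-count patients but follows them up. Section 9.1 excludes and is silent on follow-up. Section 4.3 asks for the Early Termination evaluations after withdrawal, and 7.2.6.2 includes an MRI in them, but a scan at the time of exclusion is not LVEF at 6 months. Under 8.1.3 the patient remains in the FAS by definition. Under 8.2, without a 6-month MRI, the patient adds nothing to the primary ANCOVA.

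**How much a notice could reveal**

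Let λ be the notice rate in the cell arm and rλ the rate in the placebo arm. With 1:1 allocation,

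P(active | notice) = ½λ / (½λ + ½rλ) = 1/(1 + r).

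| r (placebo rate ÷ cell-arm rate, assumed) | P(active given notice) |
|---|---|
| 1 | 0.50 |
| 0.5 | 0.67 |
| 0.25 | 0.80 |
| 0.1 | 0.91 |
| 0 | 1.00 |

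The documents do not give r. Count, depletion and viability are specified under the cell-product heading, and placebo is saline with serum (5.9.2), which argues for r below 1. Cells are selected from every patient's marrow (5.1), low-count exclusion covers both arms (4.3) and both products are made under GMP quality control (5.9), which argues against r = 0.

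**The case against.** A reader might infer that section 9.1 breaks the blind. The documents do not go that far. No section gives the monitor the allocation or says that the notice names the arm, and a quality violation can arise in either arm for the reasons just listed. A sterility finding, for example, could concern either product.

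A reader might also infer that sections 9.1 and 7.2.2 cannot both operate, that 7.2.2 already bars the monitor from these data, or that a product defect could not reach the site until the trial ends. None of this is stated. Section 7.2.2 delays a documentation step and does not mention the monitor, and the laboratory's responsible person stays primarily responsible for safety throughout.

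Other protections are real. MRI is read centrally and blinded (6.1.1, 6.1.5), as is echocardiography (6.1.2, 6.1.6). The site-graded efficacy outcomes are exploratory (8.5). The FAS definition keeps excluded patients in the confirmatory population on paper. Section 5.4 already says what follows if an Investigator is unblinded.

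This narrows the point without removing it. Section 9.1 still orders an exclusion and a message without reference to any of these rules. Central reading protects how LVEF is measured, not whether it is obtained.

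**Conclusion.** The point holds as an unreconciled rule and should be corrected. Section 9.1 creates a possible, not a certain, route to unblinding, and allows exclusion after randomization on product quality with no stated follow-up.

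The size cannot be fixed from the documents, because no rate of post-release violations is given. If notices arise almost only in the cell arm, one notice nearly reveals the arm. If both arms are judged alike, it reveals nothing. Any effect on the primary result would come through missing 6-month LVEF, not through biased reading of the scans. The conclusion rests on reading the Clinical Monitor of the product review as the monitor who attends the sites, which is the natural reading because the protocol does not separate them.

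**What to change.** 1. In section 9.1, replace exclusion from the study by an instruction to record a protocol deviation for blind review, with the patient staying in follow-up for study assessments and in the FAS. Reconcile this with the withdrawal rule for unblinded cases in section 5.4.
2. State that any product-quality notice to a site uses one allocation-neutral form, applied alike to both arms, and that the code is opened only under section 5.4.
3. State when the quality data are reviewed and by whom, so that anyone who sees allocation-revealing records during the trial is not the person monitoring site data.
4. Reconcile sections 3.3, 5.4, 5.9.3, 7.2.2 and 9.1 on what the treating physician is told. No clinical rule is proposed here.

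Items 1, 2 and 4 cost protocol wording and one form. Item 3 may need a second reviewer if an independent in-trial check is kept. Leaving that check to the laboratory alone would avoid the extra person but give up independence. That is a trade-off for the sponsor, and the point does not depend on it.

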### **9.2 Case Report Forms and Source Documentation**

All relevant data collected during the study for all of the patients enrolled in the study will be recorded in CRF. The data will be entered by the responsible Investigator or someone authorized by him in a timely manner.

The physician will confirm the completeness, correctness and plausibility of the data by his signature. All source documents from which CRF entries are derived should be placed in the patient's medical records. Measurements for which source documents are usually available include laboratory assessments, 12-lead ECG recordings, cardiac MRI scans, echocardiography and Holter.

The original data in the CRF for each patient will be checked against source documents at the study site by the clinical monitor. Additions and corrections will be dated and signed by the responsible physician or an authorized person. Reasons must be given for corrections that are not self-explanatory.

All data are stored in a central database. Instances of uninterpretable data will be discussed with the Investigator for resolution.

The original data of MRI and ECHO will be recorded directly with standardized methods and materials and stored digitally. Data will be transferred electronically to core laboratories for analyses. Analyzed data will be entered by the study personnel into the CRF.

If corrections and/or additions are needed after checking the CRF, a corresponding query must be formulated and forwarded to the physician for his response.

### **9.3 Access to Source Data**

During the course of the study, a monitor will make site visits to review protocol compliance, compare CRF and individual patient's medical records, assess drug accountability, and ensure that the study is being conducted according to pertinent regulatory requirements. CRF entries will be verified with source documentation. The review of medical records will be performed in a manner to ensure that patient confidentiality is maintained.

Checking of the CRF for completeness and clarity, and cross-checking with source documents, will be required to monitor the progress of the study. Regulatory authorities, IECs, and other authorized persons may wish to carry out source data checks and/or on-site audit inspections. Direct access to source data will be required for these inspections and audits. They will be carried out giving due consideration to data protection and medical confidentiality. The Investigator assures the Sponsor of the necessary support at all times.

### **9.4 Data Processing**

All data will be entered in a central data base.

The data-review and data-handling document, to be developed during the initiation phase of the study, will include specifications for consistency and plausibility checks on data and will also include data-handling rules for obvious data errors. Query/data correction forms for unresolved queries will be cleared for resolution with the Investigator. The database will be updated on the basis of signed corrections.

### **9.5 Archiving Study Records**

According to ICH guidelines, essential documents should be retained for a minimum of 2 years after the last approval of a marketing application in an ICH region and until there are no pending or contemplated marketing applications in an ICH region or at least 2 years have elapsed since the formal discontinuation of clinical development of the investigational product. The essential documents of this study will be retained for a longer period if required by the applicable legal requirements.

### **9.6 Good Clinical Practice**

The procedures set out in this study protocol are designed to ensure that the Sponsor and Investigators abide by the principles of the Good Clinical Practice guidelines of the ICH, and of the Declaration of Helsinki (2013). The study also will be carried out in keeping with local legal requirements.

## **9.7 Informed Consent**

Patients who are eligible for enrolment into the study will be informed by their surgeon in detail about the trial. Patients will be allowed adequate time for consideration and making an informed decision, ideally 24 hours. During this period patients will have the opportunity to discuss questions and concerns with their surgeon. In patients willing to participate in the trial, informed consent will be obtained from the patient (or his/her legally authorized representative) according to the regulatory and legal requirements of Germany. This consent form must be dated and retained by the Investigator as part of the study records. The Investigator will not undertake any investigation specifically required only for the clinical study until valid consent has been obtained. The date and time when consent was obtained will also be documented in the CRF.

According to the German Medicines Act, under-age patients must personally provide informed consent (in addition to their legal representatives) provided they are able to understand the information given to him/her in this study. This is not relevant for this study, as under age persons are excluded.

The explicit wish of a minor, or mentally incapacitated adult, who is capable of forming an opinion and assessing the study information, to refuse participation in or to be withdrawn from the study at any time will be considered by the Investigator.

Patients can withdraw their consent at any time point during the study period.

If a protocol amendment is required, the informed consent form may need to be revised to reflect the changes to the protocol. If the consent form is revised, it must be reviewed and approved by the appropriate IEC/PEI, and signed by all patients subsequently enrolled in the study as well as those currently enrolled in the study.

## **9.8 Protocol Approval and Amendment**

Before the start of the study, the study protocol and/or other relevant documents will be approved by the IEC and Competent Authorities (PEI), in accordance with German legal requirements. The Sponsor must ensure that all ethical and legal requirements have been met before the first patient is enrolled in the study.

This protocol is to be followed exactly. To alter the protocol, amendments must be written, receive approval from the appropriate personnel, and receive IEC and Competent Authority (PEI) approval prior to implementation (if appropriate).

Administrative changes (not affecting the patient benefit/risk ratio) may be made without the need for a formal amendment. All amendments will be distributed to all protocol recipients, with appropriate instructions.

